## Methods/Design

### Study design

This single-center, two-phase study will last 12 weeks. It will be a randomized, prospective, crossover, open-label study comprising two groups and two treatment sequences, each consisting of 4 weeks of daily treatments separated by a 2-week washout period (Figure 1). In total, 40 patients will be recruited (20 patients per group) from a dialysis center in Chang Gung Memorial Hospital (CGMH), Kaohsiung, Taiwan. The subjects will be randomly and equally assigned with a central registration method into group A (JBT course in period I but not in period II) or group B (JBT course not in period I but in period II). The research protocol has been approved by the Ethics Committee of the CGMH (202000477A3) and registered at ClinicalTrials.gov (NCT04417101). The Standard Protocol Items: Recommendation for Interventional Trials (SPIRIT) 2013 checklist is provided in Table 1.

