#### Primary outcome

The primary outcome used in this study will be the Kidney Disease Quality of Life 36-Item Short-Form Survey (KDQOL-36), a self-report measure developed for health-related concerns of individuals who visit dialysis facilities for treatment (29). The KDQOL-36 is available in English and was translated into Mandarin Chinese by the RAND Corporation (see: http://www.rand.org/health/surveys_tools/kdqol.html). The instrument is composed of 12 general health items and 24 kidney-specific items. The items on general health are summarized into a Physical Component Summary (PCS) score and a Mental Component Summary (MCS) score. The 24 kidney-specific items comprise three scales: symptoms and problems, burden of kidney disease, and effects of kidney disease (12, 4, and 8 items, respectively). The raw scores are transformed into a linear range of 0–100, where higher scores indicate better QOL (30).

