#### Secondary outcomes

Secondary outcome measures will include arm motor function evaluated with the Fugl-Meyer Assessment for upper extremity (FMA-UE); muscle power threshold, measured with a grip algometer; and self-reported degree of pain [Visual Analogue Scale (VAS) score].

Upper limb function will be assessed with the FMA-UE, a stroke-specific test for measuring motor impairment and recovery (31). The FMA-UE, which is widely used to evaluate upper limb motor function in patients with stroke, is often applied in studies of pain disorders in the upper extremities (32). The maximum score of the upper extremity scale is 66 points, divided among three components: shoulder–arm (36 points), wrist–hand (24 points), and coordination (6 points). The reliability and validity of the FMA-UE are excellent, and it is sufficiently sensitive for both clinical and research applications (33). The assessment will be performed in a standardized manner to differentiate the function levels of the fistula and non-fistula arms.

Handgrip strength will be measured with a digital handgrip dynamometer (TTM-YD, Tokyo, Japan). Two consecutive measurements of the fistula-side hand will be performed at an interval of 30 s, and the maximal isometric reading will be used for data analysis (34). Hand strength is used as a simple metric of general muscle strength for identifying functional deficits (35). It can also provide good resolution for localized pathologies and provides outcomes that allow better understanding of the therapeutic response of the impaired hand (36).

Pain perception will be recorded immediately after cannulation on a VAS, a non-graduated horizontal line of 100 mm where 0 = no pain at all and 100 = as painful as possible. The VAS and grip strength measures will be assessed immediately before the first treatment; at 4, 6, and 10 weeks after the first treatment; and at follow-up.

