### Statistical analysis

#### Sample size

A statistical power analysis by G^*^Power version 3.1.9.2 for the differences in the outcome measure between both groups was conducted to determine the investigated sample size to achieve adequate power (80%, α = 0.05). For repeated measures ANOVA analysis, to achieve 80% power and a 25% effect size (40), at least 34 participants will be needed. Considering a 15% loss to follow-up, we plan to recruit 40 participants (20 participants for each group) to compensate for possible dropouts.

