#### Data analyses

Both intention-to-treat (ITT) and per-protocol (PP) analyses will be applied in the present trial. Continuous data will be presented as mean ± SD, and categorical data will be presented as frequencies and proportions. The Student's *t*-test for continuous variables and chi-squared test for categorical variables will be used to compare the characteristics and clinical data of patients with and without JBT treatment. Repeated measures ANOVA will be conducted to compare the subjects' conditions over time. The Mann–Whitney U test and generalized estimating equation will be applied to compare differences when the distribution of data does not meet the assumption of normality. All analyses will be performed in IBM SPSS Statistics 22 (IBM Co., Armonk, NY, USA). A *p*-value <0.05 will be considered statistically significant.

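### The observed distribution chooses the analysis, and for repeated measures the fallback is GEE, which does not cure non-normality and, without a small-sample correction, exceeds 5% false positives with 34 to 40 patients

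*Protocol article*

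**What the plan says.** The Data analyses section of the protocol article names Student's t-test to compare patients with and without JBT, and repeated measures ANOVA to compare conditions over time. It then adds a rule that sets Mann–Whitney U beside GEE as the fallback: "generalized estimating equation will be applied to compare differences when the distribution of data does not meet the assumption of normality". The threshold throughout is a p "value <0.05 will be considered statistically significant". The section names no normality test, GEE covariance estimator, small-sample correction or tested contrast.

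The Sample size section rests on the default method, not the fallback. For repeated measures ANOVA, "to achieve 80% power and a 25% effect size (40), at least 34 participants will be needed", which 15% loss to follow-up raises to 40.

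The main scores are bounded. For the KDQOL-36, "The raw scores are transformed into a linear range of 0–100, where higher scores indicate better QOL". For the FMA-UE, "The maximum score of the upper extremity scale is 66 points". The Outcome measurement section and Table 1 schedule five assessments (weeks 0, 4, 6, 10 and 12), while the Abstract counts four.

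**The concern.** The rule is a positive instruction, so an analysis plan that followed the article would inherit it. It raises three problems.

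1. GEE does not deal with non-normality. With an identity link it compares the same means as a linear model. What it adds is a robust covariance, whose justification is large-sample. With 17 to 20 patients per sequence that covariance is biased downwards.
2. When the rule fires, it discards the method on which the trial was sized, on the strength of the trial's own data.
3. Mann–Whitney tests rank ordering between independent samples, not a mean difference. The quantity tested would then depend on the observed shape, and scores within one trial could be analysed by different methods.

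At stake are the 5% level and the width of the intervals, in the situation for which the rule was written.

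**Working it through.** **The plan's own figure.** Inputs from the Sample size section: f = 0.25 (reading the 25% effect size as Cohen's f), 80% power, α = 0.05. Assumed: two measurements (m = 2) and within-patient correlation ρ = 0.5.
- Noncentrality λ = f²·N·m/(1−ρ) = 0.0625 × 34 × 2 / 0.5 = 8.5.
- The critical F(1, 32) is 4.149, which gives power 0.807. So 34 is reproduced.
- 34/0.85 = 40. The sample size is not in dispute here.

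**Exact size of the uncorrected GEE test under normal data.** Take n patients per sequence, an identity link, a group-by-time mean model and balanced data. The sandwich covariance then uses divisor n instead of n−1, so the Wald statistic is W = T²·n/(n−1), where T² is Hotelling's two-sample statistic. With p degrees of freedom, T² is distributed as p(2n−2)/(2n−p−1) times F(p, 2n−p−1). Therefore

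P(W > χ²) = P( F(p, 2n−p−1) > χ²·[(n−1)/n]·(2n−p−1)/[p(2n−2)] ).

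Worked case, n = 20 and p = 4 (five visits): 9.488 × 0.95 × 35/(4 × 38) = 2.075, and P(F(4, 35) > 2.075) = 10.5%.

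| Test | N = 40 | N = 34 |
|---|---|---|
| 1 df (treatment contrast, or two visits) | 6.4% | 6.6% |
| 2 df | 7.6% | 8.1% |
| 3 df (four visits) | 8.9% | 9.8% |
| 4 df (five visits) | 10.5% | 11.7% |

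A 95% interval for the 1-df contrast is too narrow by the same mechanism. At N = 40 the ratio of widths is 1.960 × √(19/20)/2.024 = 0.944, about 6% too narrow. At N = 34 it is 1.960 × √(16/17)/2.037 = 0.933, about 7% too narrow.

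**Simulation with non-normal data.** There were 20,000 null trials per setting (8,000 for Mann–Whitney), with 17 or 20 patients per sequence. Correlation was compound-symmetric (0.5) or AR(1) (0.6). Data were normal, lognormal, ceiling-truncated or t with 3 df. Correlations and shapes are assumed.
- GEE, uncorrected, non-normal data: 5.9–6.5% (1 df), 7.5–9.5% (3 df), 8.6–11.7% (4 df).
- Repeated measures ANOVA, group-by-time: 4.0–5.2% under compound symmetry; 5.0–6.8% under AR(1) without a sphericity correction; 2.5–5.0% with Greenhouse–Geisser.
- Mann–Whitney between groups: 4.4–5.1%. Applied to JBT versus non-JBT periods as if they were independent samples: 0.6–1.0%, which is very conservative and so costs power.
- Whole rule (a normality pre-test chooses between ANOVA and GEE): with a Jarque–Bera pre-test and non-normal data, 5.1–5.8% over two visits and 7.0–9.3% over five. With a Shapiro pre-test and a skewed 0–100 score, 6.1–6.2% and 8.6–8.9%.

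**The case against.** The strongest reply is that the article fixes very little of what drives these figures. It names no covariance estimator, reference distribution, small-sample correction or contrast, and the full analysis plan, which is not shown, could settle them all. In a two-period crossover the natural treatment test has one degree of freedom, where the excess is one to two percentage points. The Discussion also calls the trial a pilot. These objections stand as limits on the size of the point. They do not remove it, because the switch itself is written as a rule.

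Several stronger readings are tempting, but the document does not support them.
- **That the trial has a 10–12% false-positive rate.** That figure belongs to the five-visit interaction under uncorrected GEE alone. The whole rule gives less, because ANOVA is retained whenever the pre-test does not fire.
- **That Mann–Whitney also inflates error.** It does not. Its faults are the changed quantity and, if pairing is ignored, the lost power.
- **That the abandoned method always keeps 5%.** Repeated measures ANOVA does so under sphericity or with a correction. The visits are unequally spaced, and under AR(1) the uncorrected test reached 6.8%.
- **That the switch gives up a planned within-patient t-test.** The article names only a t-test comparing patients with and without JBT.
- **That the trigger will probably fire.** For assumed non-normal shapes, the pre-tests fired in about half to nine-tenths of simulated trials. The article gives no distributional data for its scores, and a bounded score need not be markedly skewed.

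**Conclusion.** The concern holds, at moderate severity. A normality-triggered move to GEE replaces a roughly valid method with an anticonservative one. The excess is small for a treatment contrast, where the rate is about 6–7%. It is material for multi-visit tests: about 9–10% over four visits and 10–12% over five under normal data, and slightly lower in most non-normal settings. The rule as a whole gives roughly 6–9%, against about 5% or less for repeated measures ANOVA with a sphericity correction.

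The GEE figures assume the robust covariance, a chi-square reference, no small-sample correction and complete, balanced data. The rates for the whole rule depend further on the assumed shapes and pre-test. Independently of these figures, the article lets the observed distribution decide both the method and the quantity tested.

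**What to change.** Delete the normality-triggered switch and fix one method per outcome in advance, whatever the distribution. Two suitable choices are:
- a linear mixed model with small-sample degrees of freedom; or
- a t-test on within-patient period differences, compared between the two sequences.

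Add a permutation test that re-shuffles sequence labels as the distribution-free sensitivity analysis. It relies on the randomisation and not on normality. If GEE is kept for any outcome, require a bias-corrected covariance with a t or F reference. If repeated measures ANOVA is kept, state the sphericity correction.

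The cost is analysis wording only, with no new data or visits. The downside is that p-values and intervals will be slightly less favourable than uncorrected GEE would give.

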## Discussion

Repeated myofascial pain in the fistula arm during HD sessions is a distressing symptom reported by patients receiving HD. Due to a lack of reporting in the past, this type of pain related to the fistula arm is rarely treated sufficiently to meet the needs of these patients. Uncontrolled pain in the affected muscles can degrade QOL and cause non-adherence to the recommended dialysis regimen, which can in turn increase the mortality rate due to consequent cardiovascular and pulmonary events (41, 42). Juan Bi Tang therapy uses an ancient herbal medicine to address these painful experiences, especially the inadequate flow of *qi* and blood. In a previous study, compared to Western medicine, JBT was found to be safe and particularly beneficial to arthritis patients with the cold and deficiency pattern (37). Most patients who receive HD have low physical performance and low immunity (43), and researchers have found that a feature of the TCM pattern in patients receiving HD is mainly deficiency syndrome (44). The etiology of TCM pays attention to the circulation of *qi* and blood, and insufficient or blocked circulation will cause pain. Juan Bi Tang is used clinically to treat painful obstruction of *qi* and blood deficiency. Thus, we propose the first pilot crossover trial to examine the effectiveness of JBT therapy in alleviating dialysis-related myofascial pain around the fistula arm in patients receiving HD.

At present, the findings of most animal studies have confirmed the benefits of JBT in improving arthritis and synovitis (45–47). Significant reductions in the serum levels of MMP-2 and MMP-9 indicate that JBT has a role to play in preventing osteoarthritis (45). Similar effects of JBT on synovial inflammation and bone destruction through inhibiting the pro-inflammatory cytokines have recently been reported by Wang et al. (46). In addition, a study by Zhao et al. has demonstrated that JBT ameliorates bone destruction and reduces bone loss induced by rheumatoid arthritis (47). Therefore, it is possible that JBT may alleviate pain by not only improving blood flow but also down-regulating inflammatory markers. This study is designed to determine whether JBT is preferable to non-pharmacologic methods for the treatment of dialysis-related myofascial pain. If this trial produces the expected results, it will provide both patients and physicians an additional option for pain control. Moreover, this trial will provide preliminary data on the effects of JBT on arm power and motor function, QOL, and safety.

HD patients may receive 10–12 medications daily, and many of these medications require multiple doses each day. Drug–drug interactions are very common due to poly-pharmacy in HD patients (48), so the involvement of JBT therapy in drug interactions is an important issue for the therapeutic efficacy and safety of medical treatment. Although several studies have reported the possibility of herb–drug interactions in CKD patients leading to nephrotoxicity, electrolyte abnormalities, or changes in kidney hemodynamics (49, 50), very few studies have tested CHM with targeted safety assessments. It is worth noting that the *Rx. Angelica Sinensis* component of JBT may increase the risk of bleeding when heparin is used to prevent clotting in the dialytic extracorporeal circuit (51). In addition, excessive intake of *Rx. Glycyrrhizae Preparata* may lead to hypertension, hypokalemia, and metabolic alkalosis (52), which may cause myopathy and arrhythmia in HD patients. Thus, the results will contribute to herb repurposing for managing myofascial pain in patients receiving HD and will provide information useful for designing a large-scale randomized controlled trial in the future.

The strengths of this study include: (1) This study is the first pilot randomized cross-over trial to evaluate the feasibility of JBT for the treatment of dialysis-related myofascial pain. (2) The design of the trial is based on TCM syndromes because dialysis-relayed myofascial pain can be inferred to inadequate *qi* and blood around the fistula arm in patients receiving hemodialysis. (3) The study of different safe and lower cost can be considered for scientific use of techniques related to TCM in dialytic patients. Nevertheless, a few study limitations should be noted. First, this study will be an open-label study because of the difficulty of preparing a suitable placebo; the pharmaceutical technology of CHM powder does not yet allow such a process because of the distinctive colors, tastes and smells of the preparations (51). Moreover, due to the use of patient-reported outcomes, the reliability of the conclusions of the study may be reduced due to the absence of participant blinding. Second, it will be a crossover trial and thus may entail possible carryover effects. The component of JBT with the longest half-life is *Rx. et Rz. Notopterygii* (*T*_1/2_ = 190–768 min); however, its washout period is only 64 h (52). To minimize this possibility, we have designed a 2-week washout period between the two groups. However, no data on the length of the washout period of JBT are currently available. The washout period involves the biological half-lives of multiple herbs and changes in the pharmacokinetics of the CHM formula (53). In the event of carry-over effects, only data from the first period will be used for the analysis, for it is a randomized parallel-group design. The current sample size was calculated on the basis of a single period of data alone; thus, the estimated size will be sufficient for specific analysis. Third, the non-treatment and JBT treatment periods will be only 4 weeks.

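### Switching to first-period data if carry-over appears lets the trial's own data choose the analysis, with no adjustment of the 0.05 threshold

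*Protocol article*

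**What the plan says.** The trial is a two-sequence crossover: "group A (JBT course in period I but not in period II) or group B (JBT course not in period I but in period II". Outcomes are measured at weeks 0, 4, 6 and 10 and at follow-up, so each period has a baseline and an end value (Outcome measurement; Table 1).

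The Discussion accepts that carry-over is possible. It reports a 64-hour washout for the component with the longest half-life and sets a 2-week gap. It then concedes: "However, no data on the length of the washout period of JBT are currently available". The rule follows: "In the event of carry-over effects, only data from the first period will be used for the analysis". The reason given is that period I on its own compares two randomised groups in parallel. The next sentence defends the rule by saying that the sample size rests on one period's data and is therefore adequate.

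The Data analyses section names repeated measures ANOVA, with alternatives for non-normal data. A p-value below 0.05 "will be considered statistically significant". It names no carry-over test, no threshold for one, and no adjustment for choosing between two analyses.

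**The concern.** A carry-over event can be recognised only from this trial's outcomes, because the protocol cites no other source. The rule is therefore a preliminary test followed by one of two analyses.

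The difficulty is that the preliminary test and the first-period comparison can share information. The usual carry-over contrast compares patient totals over the two periods between sequences, and those totals contain the week-4 values. When the pre-test is positive by chance, the week-4 difference tends to be large already, yet it is then tested at the full 0.05.

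Two things are at stake. The stated significance level may not be the error rate of the procedure actually followed. And the rule may give little protection against the carry-over it is meant to handle.

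**Working it through.** **Inputs from the document.** The Sample size section plans "to determine the investigated sample size to achieve adequate power (80%, α = 0.05"), then "to achieve 80% power and a 25% effect size (40), at least 34 participants will be needed". It adds: "Considering a 15% loss to follow-up, we plan to recruit 40 participants (20 participants for each group").

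**The plan's own figure.** Read 25% as f = 0.25, with 2 groups, m = 2 time points and correlation ρ = 0.5 (these readings are assumptions). Noncentrality is f²·N·m/(1−ρ) = 0.0625 × 34 × 2 / 0.5 = 8.5. On F(1, 32) this gives power 0.807, so 34 reproduces. Then 34 / 0.85 = 40, and 40 × 0.85 / 2 = 17 completers per sequence.

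**Assumptions for the check.** Normal outcomes with SD 1, ρ of 0.5 or 0.7 between visits, a two-sided pre-test at 5% or 10%, and two-sided treatment tests at 5%. None of these except the 0.05 level is in the document.

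**Why the two tests are linked.** With totals as the carry-over measure, corr(Y1 + Y2, Y1) = √((1+ρ)/2). This is 0.87 at ρ = 0.5 and 0.92 at ρ = 0.7.

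**Type I error, totals pre-test** (simulation, no treatment effect, no carry-over, 17 per sequence):

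| ρ | Pre-test level | First-period false rejection after a positive pre-test | Overall type I error |
|---|---|---|---|
| 0.5 | 5% | 52% | 7.3% |
| 0.5 | 10% | 36–37% | 8.1% |
| 0.7 | 5% | 63% | 7.9% |
| 0.7 | 10% | 42–43% | 8.7% |

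The last column follows from the third, because totals and within-patient differences are independent here. For ρ = 0.7 and a 5% pre-test: 0.05 × 0.633 + 0.95 × 0.05 = 0.079. Either analysis used unconditionally stays at 4.9% to 5.1%.

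**Type I error, week-6 pre-tests** (same settings):
- Raw week-6 values, then end-of-period values: 5.5% to 6.9%.
- Week 6 minus week 0, then change scores in period I or the end-of-period crossover: 5.5% to 5.9%.
- The same pre-test, with change scores in both analyses: 3.8% to 4.2%, below nominal.

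**Detecting a true carry-over of 0.25 SD.** For totals at ρ = 0.5, the standard error is √(2(1+ρ)) × √(2/17) = 1.732 × 0.343 = 0.594. The standardised shift is 0.25 / 0.594 = 0.42. That gives power of about 7% (5% level) to 13% (10% level). For raw week-6 values the standard error is 0.343 and the shift 0.73, giving about 11% to 18%. For week 6 minus week 0 at ρ = 0.7 and the 10% level it reaches 24%.

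**Bias.** Let carry-over c act in the JBT-first sequence. The two-period estimate is [(τ − c) − (−τ)]/2 = τ − c/2. With τ = 0.50 and c = 0.25 it is 0.375. With the totals pre-test, 20 per sequence and ρ = 0.5:
- First-period estimate, when the rule selects it: 0.80 to 0.89.
- Average over the whole procedure: 0.41 to 0.43.
- First-period estimate always used: 0.50.

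**Precision of the two candidates** (17 per sequence, ρ = 0.5). The two-period standard error is √((1−ρ)/17) = 0.17 SD. For week 4 adjusted for week 0 it is √(2/17) × √(1−ρ²) = 0.343 × 0.866 = 0.30 SD.

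**The case against.** The strongest reply is that the protocol never calls this a two-stage procedure and names no test. With a baseline scheduled at week 6, a week-6 check is at least as natural as a test on totals, and an analysis plan not shown may specify it. This stands. A reader might infer that the type I error is certainly raised, but the document does not support that. Under week-6 checks the excess is small, and in one variant there is none.

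A reader might also infer that real carry-over would almost never be found. That too goes beyond the document. With a week-6 check at the 10% level, a carry-over of 0.5 SD is found about 41% to 59% of the time and 0.8 SD about 73% to 91%. The low figures apply to small carry-over and to the totals test.

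A third inference is that the selected estimate is always pushed away from zero. It is not. It moves in the direction of the carry-over signal. With a true effect of 0.50 SD and carry-over of −0.25 SD, the selected estimate averages only 0.11 to 0.20 SD (totals pre-test, 20 per sequence, ρ = 0.5). If true carry-over is zero, the shifts cancel on average.

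The protocol's own defence, that the sample size rests on one period, does not answer the point. It concerns power, whereas the problem is selection. Randomisation protects a period I comparison fixed in advance, not one chosen after a correlated test.

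The 2-week gap is 336 h, or 336 / 64 = 5.25 times the quoted washout, which makes carry-over less likely. But then a positive pre-test is more often a chance finding, and the authors themselves say that the washout of the full formula is unknown.

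Finally, the trial describes itself as a pilot yielding preliminary data. That lowers the severity without removing the defect.

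**Conclusion.** The concern holds in a conditional form. What is certain from the text is that the choice of analysis depends on the trial's data and that no adjustment is stated. What is not certain is the size of the error.

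For 17 per sequence, assumed correlation 0.5 to 0.7 and a pre-test at 5% to 10%:
- With the totals test the overall type I error is about 7% to 9%, and roughly 36% to 63% of first-period tests reject falsely after a chance-positive pre-test.
- With week-6 tests the overall error is about 5.5% to 7%, or about 4% in one change-score variant.
- A carry-over of 0.25 SD is mostly missed under either approach.

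Leaving the test open adds its own risk, because in an open-label trial with a self-reported primary outcome the check could be chosen after results are seen. This is a should-fix point, not a fatal one.

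**What to change.** Delete the conditional rule from the Discussion. In Data analyses, fix one primary analysis that does not depend on any carry-over test. Either choice is valid:

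- The two-period within-patient analysis, with a statement that true carry-over c biases it by about c/2 (towards zero if c acts in the same direction as the effect).
- The first-period comparison, week 4 adjusted for week 0, with a statement of its lower power. Under the assumptions above its standard error is about 0.30 / 0.17 ≈ 1.7 times that of the two-period analysis. As a guide, an unadjusted week-4 comparison has about 29% power for a 0.5 SD difference with 17 per group, and 34% with 20.

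Always report the other analysis as a sensitivity analysis with its confidence interval. Show week 6 against week 0 by sequence descriptively, as the check on washout.

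All the assessments needed are already scheduled, so the change is one of wording. The cost is the loss of the automatic fallback, plus the bias or power cost of whichever primary analysis is chosen.
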